## 5.2 Exclusion Criteria

| - Pregnant or breastfeeding - Unwilling to use acceptable birth control - Unable to consent for research - Unwilling to avoid other cannabis products - Daily cannabis use - History of psychotic episode, psychosis, or active suicidality - Diagnosis of substance use disorder - Severe cardiovascular disease (MI, PTCA, unstable angina, CABG, and/or serious arrhythmia in the previous 6 months |
| --- |

## 5.3 Lifestyle Considerations

Subjects must avoid using all cannabinoid containing substances throughout the study period. Subjects who endorse cannabinoid use other than dronabinol should consider early withdrawal from the study.

## 5.4 Screen Failures

Screen failures who fail due to positive urine test for cannabinoids may rescreen up to 3 times at least 2 weeks from date of last screen failure.

Screen failures who fail due to lack of chronic pain or insufficient pain impact score may rescreen in 3 months from date of screen failure.

## 5.5 Strategies for Recruitment and Retention

**Recruitment strategy.** Recruitment will be active and passive. Active recruitment will focus on contacting potentially eligible adults with SCD who are treated at Mt. Sinai’s outpatient and inpatient practices and inviting them to participate. We will employ the following recruitment strategies:

1. Referrals from providers. Patients who are seen for in-person or telemedicine visits with providers in the Sickle Cell Program and are potentially eligible will be referred to study coordinators.
2. Advertising in clinical area. Flyers and brochures about the study will be posted in facilities where adults with SCD are treated
3. Community outreach. We will engage community-based organizations and community leaders to optimize community outreach including events such as health fairs and Sickle Cell Awareness Day events and via advertising the study over email and social media. This will be facilitated through existing partnerships with the Sickle Cell Thalassemia Patients Network and the New York chapter of the Sickle Cell Association of America.

**Feasibility of recruitment.** Recruitment will be feasible. We will primarily recruit patients treated for SCD at the Mount Sinai Adult Sickle Cell Center. Approximately 40 unique patients are seen in clinic each month.  Of approximately 450 adults with SCD treated at the Center we estimate half (225) will have chronic pain, of those 25% will be frequent cannabis users and this ineligible for our study (approximately 56) so we estimate we will have approximately 169 eligible patients. However, we have also created a plan for regularly monitoring recruitment and implementing a contingency plan of expanding to additional NYC Sickle Cell programs if needed.

**Recruitment timeline.** We will recruit for 36 months (see Project Timeline), enrolling 2-3 subjects per month. Recruitment will be feasible; based on the numbers above and prior studies, we expect to identify 30-45 potentially eligible individuals per month, screen 33% of those (10-15), and enroll 20% of these screened (2-3 per month). To monitor progress towards prespecified recruitment benchmarks will be examined at each quarter (3m period).

**Recruitment monitoring.** We will monitor recruitment and enrollment every week using flowcharts of potential subjects who are identified, screened, enrolled, randomized, and certified for medical cannabis. As we do for our other studies, we will review these data at weekly research meetings of the study team, discuss barriers or issues, and institute corrective measures if needed in an ongoing way, such as increasing outreach, letters, and telephone calls. In addition to routine weekly monitoring, we will assess our progress against the specific benchmarks on the schedule described in the Table above, first after 3 months then every 6 months. Recruitment reports will be included in reports to the Data and Safety Monitoring Committee (DSMC) every 6 months.

**Contingency plan.** We expect to meet benchmarks at Mt. Sinai. However, if enrollment falls below 75% of targets in two subsequent quarters, we will activate our contingency plan of recruiting from other New York City Sickle Cell centers. This plan is feasible due to membership in the American Society of Hematology (ASH) Research Consortium Clinical Trials Network of New York City. It is premature to describe details of possible expansion to additional sites.

# 6 Study Intervention

## 6.1 Study Intervention(s) Administration

### 6.1.1 Study Intervention Description

Dronabinol is a synthetic form of 9-D-tetrahydrocannabinol (THC), the most common cannabinoid found in most strains of marijuana. 37 Dronabinol binds both of the known receptors of the endocannabinoid system, CB1, which is located primarily in the nervous system, and CB2, which is located primarily on immune cells.19,38 Dronabinol is a commercially available, Schedule III medication that is currently FDA approved for the treatment of chemotherapy induced nausea and vomiting and for appetite stimulation in patients with AIDS.37,39-41 As such, legal use of dronabinol in research is feasible; indeed, one of us has published a study of dronabinol effects in an human experimental pain model. 42 Dronabinol has been or currently is being studied for control of pain, including neuropathic pain, in diverse disorders, and control of inflammation, especially in inflammatory neurological and gastro-intestinal disorders.17,20,43-48 Although patient blinding is imperfect due to subject recognition of euphoric effects, in many of these studies a placebo- controlled design has resulted in interpretable results.

The schedule is dronabinol/placebo twice daily (approximately upon awakening and 8-12 hours later). Doses should be taken with consistent timing but without regard to meals. All doses will be administered using dronabinol 5 mg/placebo capsules. The starting dose in all subjects is dronabinol/placebo is 5 mg twice daily up to a total of 10 mg a day. Study agent will be dispensed in quantities adequate for two weeks of dosing. All discussions with subjects about dosing will be conducted in terms of numbers of capsules, not mg amounts.

### 6.1.2 Dosing and Administration

Dose titration will be undertaken to identify a subject-specific maximum well tolerated dose (MWTD). MWTD for dose titration will be defined as the maximum dose at which the subject feels there are no intolerable adverse effects.  On Days 2-4, a study team clinician (doctor or nurse) will initiate telephone or face to face contact with the subject to review the dosing goal – identification of a MWTD -- and then determine an agreed-on dose going forward based upon the subject’s experience to date.

**Dosing Schema:**

Day 1: Dronabinol/placebo 2 capsules twice daily.

Day 2: All subjects will have been on a dose of one capsules twice daily.

Options:

- Dose escalate to two capsules twice daily, or
- Withdraw from study if dose is intolerable

Day 3: Subjects will have been on a dose of two capsules twice daily or one capsule twice daily.

Options for subjects on two capsules twice daily:

- - Stay at two capsules twice daily
  - Return to one capsule twice daily.

Options for subjects on one capsule twice daily:

- - Declare one capsule twice daily the MWTD, or
  - Discontinue subject as dronabinol

Upon declaration of a MWTD, subjects will be instructed not to exceed the MWTD dose. Subjects will be encouraged to continue at the MWTD for the duration of the dosing period, but not at the expense of unpleasant side effects, in which case subjects may choose to take less. Subsequent upward adjustments of the declared MWTD, not to exceed four capsules twice daily, are permissible when agreed upon by a subject and study team clinician.

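### The Day 2 titration step offers no option to stay at one capsule twice daily, and the Day 1 line prints twice the starting dose

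*Protocol*

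**What the plan says.** The Dosing Schema in Protocol section 6.1.2 runs day by day:

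- Day 1: "Day 1: Dronabinol/placebo 2 capsules twice daily".
- Day 2, starting position: "All subjects will have been on a dose of one capsules twice daily". Two options follow: "Dose escalate to two capsules twice daily, or" then "Withdraw from study if dose is intolerable".
- Day 3, starting position: "Subjects will have been on a dose of two capsules twice daily or one capsule twice daily". Subjects on two capsules may stay there or "Return to one capsule twice daily". Subjects on one capsule have their own pair of options, the first being "Declare one capsule twice daily the MWTD, or" and the second discontinuation.

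Other sections bear on the same step. Section 4.3 starts all participants at 5 mg twice daily, makes the increase to 10 mg twice daily depend on good tolerance, and sets the individualized range at 5 to 10 mg twice daily. Section 6.1.1 states that only 5 mg capsules are used and gives the start as follows: "The starting dose in all subjects is dronabinol/placebo is 5 mg twice daily up to a total of 10 mg a day". The text introducing the schema in 6.1.2 has a clinician contact the subject on Days 2-4 and settle a dose by agreement. It defines the maximum well tolerated dose (MWTD) by the absence of intolerable effects.

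**The concern.** The Day 2 list is closed, and its two choices do not produce one of the two groups that Day 3 describes. Staff who work from the list would escalate a subject with bothersome but bearable effects. Staff who work from the introductory text could agree to hold that subject at one capsule, which the list does not offer. The same subject can therefore be handled in two ways in the first days on a psychoactive drug. Section 2.3.1 names treatment start and dose change as times when blood pressure may shift, and warns of added sedation and confusion with opioids, which section 5.1 allows at a stable dose.

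The Day 1 line adds to the problem. Followed as printed, it starts subjects at twice the intended dose. Both errors push early exposure upward. Section 6.1.1 requires dosing to be discussed with subjects in numbers of capsules, which are the units of the schema, so a wrong capsule count can pass straight into practice.

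**Working it through.** **Tracing the listed steps**

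| Point in titration | What the schema states | What the listed options can produce |
|---|---|---|
| Entering Day 2 | all on one capsule twice daily | – |
| Day 2 options | escalate, or withdraw | two capsules twice daily, or withdrawn |
| Entering Day 3 | two capsules or one capsule twice daily | two capsules twice daily only |

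No listed Day 2 option leads to the one-capsule group at Day 3. The only listed route back to one capsule is the Day 3 step-down, for subjects already taking two. With a stay option on Day 2, the reachable states become two capsules, one capsule or withdrawn, which matches the Day 3 line.

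**Size of the excess exposure**

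Inputs: capsule strength 5 mg (section 6.1.1); maximum 10 mg twice daily (section 4.3).

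Daily dose = capsules per intake × 5 mg × 2 intakes:

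- one capsule twice daily: 1 × 5 × 2 = 10 mg/day
- two capsules twice daily: 2 × 5 × 2 = 20 mg/day
- section 4.3 maximum: 10 × 2 = 20 mg/day

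The comparison is a subject who would hold at one capsule through Days 1 and 2: 10 + 10 = 20 mg.

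*Reading A: Day 1 at one capsule twice daily, as the Day 2 line and sections 4.3 and 6.1.1 have it.* Listed path: 10 + 20 = 30 mg. Excess: 30 − 20 = 10 mg (two capsules), over about one day.

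*Reading B: Day 1 as printed, two capsules twice daily.* The Day 2 escalation is then no change. Listed path: 20 + 20 = 40 mg. Excess: 40 − 20 = 20 mg, of which 10 mg comes from the Day 1 line and 10 mg from the missing stay option.

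Neither reading passes 20 mg/day. The excess is drug exposure in the dronabinol arm only; placebo subjects take extra inert capsules. The protocol gives no rate of subjects who would prefer to hold, so the number affected cannot be estimated.

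**The case against.** The strongest reply is that the schema should be read as a whole. The Day 3 line presupposes that some subjects held at one capsule, the introductory text lets clinician and subject agree the dose, and section 4.3 makes the increase conditional. Section 8.3.5 lets patient and investigator decide jointly to lower the dose for patient-reported grade 1 or 2 events and stops study agent for events of grade 3 or above. With only two titration levels and an MWTD defined by the absence of intolerable effects, trying the second level in a subject who can bear the first is also a reasonable way to find the maximum. On this view the omission is an incomplete list with an obvious intent, and the Day 1 misprint is a separate matter.

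Much of this stands. Forced escalation is not the intended design, and the safeguards limit the harm. Only 10 mg of the 20 mg in Reading B belongs to the missing option. But general discretion beside a closed two-item list is what creates the two ways of handling the same subject; it does not correct the list. The freedom to take less is written for the period after an MWTD has been declared, which is later than Day 2. None of these provisions corrects the Day 1 starting dose.

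The 20 mg/day ceiling used here is that of section 4.3. Section 6.1.1 gives a total of 10 mg a day, and the end of the schema allows later increases up to four capsules twice daily. Those conflicts are separate from this point, and the edit proposed here does not settle them.

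**Conclusion.** The schema is wrong as written in two places. The Day 2 options cannot produce the one-capsule group that Day 3 describes, and the Day 1 line contradicts both the Day 2 line and the starting dose given in sections 4.3 and 6.1.1. The Day 1 error is the more clear-cut of the two.

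The consequence is minor: for a subject on active drug who would have held, 10 mg of excess over about one day, or 20 mg over Days 1-2 if Day 1 is followed as printed. This occurs during planned clinician contact, with a Day 3 step-down available. These figures assume 5 mg capsules, full adherence to the listed steps, and the section 4.3 maximum as the operative ceiling. The conclusion does not depend on whether the tolerance condition in section 4.3 is stricter than the MWTD definition in 6.1.2. The final doses available do not change, and no effect on the primary endpoint or power is claimed. It should be corrected because it concerns dosing in the first days of exposure and the intended rule is clear.

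**What to change.** Give Day 2 three options:

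1. Escalate to two capsules twice daily if one capsule twice daily has been well tolerated, in line with section 4.3.
2. Stay at one capsule twice daily if subject and clinician agree not to escalate. This leads to the existing Day 3 one-capsule branch.
3. Stop if the dose is intolerable.

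In the same edit, change the Day 1 line to one capsule twice daily.

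The cost is one added bullet, one added condition and one corrected number, made through a protocol amendment and carried over to any titration contact form. No extra visits or contacts are needed.

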# 7 Study Intervention Discontinuation and Participant Discontinuation/Withdrawal

## 7.1 Discontinuation of Study Intervention

For serious adverse events (SAEs), defined as those which result in death, are life-threatening, require inpatient hospitalization or prolongation of existing hospitalization, result in significant disability or incapacity, or result in congenital anomaly or birth defect, [name] will be notified and if the event is determined to be possibly related to dronabinol it will be discontinued.  Dronabinol will not be discontinued for SAEs determined to be unrelated to dronabinol, such as pain crisis. In the event that a participant withdraws from the study or discontinues dronabinol due to a SAE, the participant’s ongoing status will be monitored by [name] until: 1) a resolution is reached, i.e., the problem requiring hospitalization has resolved or stabilized with no further changes anticipated; 2) the SAE is determined to be clearly unrelated to study intervention; or 3) the SAE results in death. In cases where a participant discontinues dronabinol for any reason, the Study

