 Coordinator will ask the participant to continue to attend all study visits and complete assessments. Criteria for discontinuation of the randomization condition include 1) pregnancy; 2) current suicidal ideation with plan or intent; 3) suicide attempt; 4) severe anxiety episode, severe depression episode, or psychotic symptoms; 5) severe adverse events probably or definitely related to the randomization condition, as defined above; 6) adverse events that have the potential to cause serious impairment of health, including ischemic or arrhythmic adverse cardiovascular disease events (e.g., myocardial infarction, unstable angina, coronary revascularization, coronary artery disease, unstable arrhythmias, transient ischemic attack, stroke, or congestive heart failure); 7) serious adverse events, defined as those which result in death, are life threatening, require inpatient hospitalization or prolongation of existing hospitalization, result in significant disability or incapacity, or result in congenital anomaly or birth defect; or 8) the request of participants or their treating providers. [name] or the Study Coordinator will be responsible for informing the participant to discontinue the randomization condition and will ask the participant to continue to attend all study visits. Once the randomization condition has been discontinued it will be for the duration of the study.

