## 7.2 Participant Discontinuation/Withdrawal from the Study

Subjects may discontinue participation at any time by informing an investigator, but there is no plan to discard previously acquired data. Subjects experiencing study agent related adverse events will be encouraged to continue study follow-up until resolution, if feasible.

A subject’s participation may be discontinued at any time by any of the investigators if discontinuation is thought to be in the subject’s best interest, if continued participation is unlikely to yield further useful data due to noncompliance with study procedures, or if the study is discontinued.

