## 9.2 Sample Size Determination

In a study examining the responsiveness of PROMIS pain impact to changes in chronic pain patients who stated pain was a “little better” had an average increase of 1.8 point with a SD of 6.6 points and “much better” was associated with an average increase of 6.8 points with a SD of 6.5 points.^65^  Based on this we have chosen a change of 5 points as representing a clinically meaningful improvement in chronic pain, with an estimated a SD of 6.5 points. With a sample size of 28 patients (56 total) in each group we will have 80% power to detect a difference of 5 points in change between two groups in pain impact score from baseline at a two-sided 0.05 significance level.

We have a strong track record of following subjects with chronic pain, opioid use, and SCD in ourprior SCD studies have achieved 85-100% retention at 6 months. In our pilot trial we approached 27 patients to enroll 6 on study, we therefore estimate if we approach 280 patients, we can enroll 70. We conservatively estimate a 20% attrition rate, so we will aim to approach 280 patients to enroll 70 to ensure 56 participants completing the study.

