## 9.3 Populations for Analyses

Primary analysis of all endpoints will be an intention to treat analysis.  Secondary analysis will be done removing patients who do not complete at least 4 weeks on study as well as any patients whose urine samples show presence of cannabinoid metabolites other than THC or whose pill counts reveal they took less than 50% of the reported optimized dose.   Safety analysis will be done on all patients who took at least one dose of the study medication.

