### 9.4.2 Analysis of the Primary Efficacy Endpoint(s)

We will examine change in pain and quality of life measures from each participant’s own baseline after 8 weeks of treatment (difference in differences analysis). Median change from baseline of patients on dronabinol will be compared to median change from baseline of patients on placebo. We have chosen to compare change from baseline between the two groups to account for heterogeneity in cause and severity of chronic pain at baseline seen in people with SCD. Comparisons of change from baseline to end of study between patients on placebo and dronabinol will be done using a Rank Sum test. A backward stepwise multivariate regression analysis will be performed to assess for covariates associated with the primary and secondary outcomes.  As the group size will be small a regression analysis will also be done to assess if any covariates associated with the outcomes are significantly difference between the study groups.

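### The Day-2 dosing schema sends participants who cannot tolerate study drug out of the study, while Section 7.1 keeps them in follow-up; the intention-to-treat comparison depends on which text is followed

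*Protocol*

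**What the plan says.** **Routes out of the study.** In the dosing schema (Section 6.1.2) a participant on Day 2 has two options: go up in dose, or "Withdraw from study if dose is intolerable". The exit is from the study, not from the drug. Section 5.3 adds: "Subjects who endorse cannabinoid use other than dronabinol should consider early withdrawal from the study". Section 7.2 lets an investigator end participation "if continued participation is unlikely to yield further useful data due to noncompliance with study procedures". For participants with drug-related adverse events, it encourages follow-up only until the event resolves, which need not be week 8.

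**Instruction to stay.** Section 7.1 applies to anyone who stops drug, whatever the reason, and says: "Coordinator will ask the participant to continue to attend all study visits and complete assessments". After its list of discontinuation criteria, the same section repeats that participants will be asked to keep attending all visits.

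**Analysis.** Section 9.3 states: "Primary analysis of all endpoints will be an intention to treat analysis". Section 9.4.1 adds that this follows group allocation and uses data from baseline to week 8. Section 9.4.2 fixes the primary test: "Comparisons of change from baseline to end of study between patients on placebo and dronabinol will be done using a Rank Sum test". Participants with other cannabinoids in their samples, low pill counts or under four weeks on study are removed only from the secondary analysis (Sections 9.3 and 9.4.1). The PROMIS pain score is scheduled at baseline, week 4 and week 8 (Sections 1.3 and 8.1). Section 9.2 enrols 70 "to ensure 56 participants completing the study".

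**The concern.** Two sections give different instructions for the same participant. Someone who cannot tolerate the drug on Day 2 leaves the study under the schema, and stays in follow-up to week 8 under Section 7.1. Staff following one text or the other would end up with different week-8 data.

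The difference matters because the loss is unlikely to be balanced. The safety hypothesis in Section 9.1 expects more low-grade adverse events, such as dizziness and nausea, on dronabinol. An exit triggered by intolerance should therefore remove more participants from that arm. If those participants would have had a different pain outcome from the ones who stay, comparing the remainder no longer has the protection of randomisation, whatever the analysis is called. A participant who leaves on Day 2 has neither a week-4 nor a week-8 score, so the measurement cannot be recovered later.

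**Working it through.** **1. The plan's own figure.** Inputs from Section 9.2: difference 5 points, SD 6.5, two-sided alpha 0.05, power 80%.

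- Normal approximation: n per arm = 2 × (1.960 + 0.842)² × 6.5² / 5² = 26.5, so 27.
- The t-test calculation gives 27.5, so 28 per arm. Power at 28 per arm is 80.7%.
- Allowance for 20% attrition: 56 / 0.80 = 70.

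The stated sizes reproduce. The 80% is power with 56 participants supplying a week-8 score. If all 70 did so (35 per arm), t-test power would be 88.7%, provided the effect stays at 5 points when participants off drug are included.

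**2. Imbalance alone.** If the 14 losses fall 10 on dronabinol and 4 on placebo, t-test power is 80.2%; with 12 and 2 it is 79.4%. Uneven loss costs little power. The risk is bias.

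**3. Size of the bias, under assumptions.** The protocol gives no loss rate by arm, so the following are assumptions: d of 35 dronabinol participants are lost; on average they would have done D points worse than that arm's completers; placebo losses are uninformative. Then

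bias in favour of dronabinol = (d / 35) × D.

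D is taken as 2 to 6.5, the upper end being one planned SD. The splits below all use the full allowance of 70 − 56 = 14 losses. The last column is the simulated two-sided type I error of the rank-sum test when the true mean difference over all 70 is zero (normal data, SD 6.5, 20,000 runs each).

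| Lost, dronabinol / placebo | Bias at D = 2 | Bias at D = 6.5 | Type I error, D = 2 to 6.5 |
|---|---|---|---|
| 7 / 7 | 7/35 × 2 = 0.4 | 7/35 × 6.5 = 1.3 | 5.7% to 10.6% |
| 10 / 4 | 10/35 × 2 = 0.6 | 10/35 × 6.5 = 1.9 | 5.8% to 17.5% |
| 12 / 2 | 12/35 × 2 = 0.7 | 12/35 × 6.5 = 2.2 | 6.5% to 21.7% |

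With 7 / 7 lost and D = 0 the simulated error is 4.9%, so the excess comes from the informative loss.

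**4. Smaller losses.** Each dronabinol participant lost adds D / 35, which is 2/35 = 0.06 to 6.5/35 = 0.19 points. If only three left for intolerance, the bias would be 0.2 to 0.6 points.

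**5. Informative placebo losses.** If the p lost placebo participants would also have done worse than their arm's completers, by D′, the net bias is (d/35) × D − (p/35) × D′. With 7 lost in each arm and D = D′, this is zero.

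**The case against.** The strongest reply is that the protocol already holds the right principle. Section 7.1 covers discontinuation for any reason and states the request to keep attending twice, whereas the schema line is one option on one day. The Day-3 option is loosely worded too, and its last item appears unfinished, so the schema may simply not distinguish leaving drug from leaving the study. This stands in part: the text conflicts, and does not settle that participants will be lost. It does not remove the need to reconcile, since the dosing schema is what staff will consult on Day 2.

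Second, losses may be few. Section 9.2 reports 85-100% retention in earlier studies and calls 20% conservative, Section 7.3 sets a 90% benchmark, and all six pilot participants completed. This stands as a limit on size. The pilot was small, though, with 14-day treatment phases.

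Third, missing-data handling may sit in a statistical analysis plan that is not shown, and a rank-sum test can accommodate imputed or worst-rank values. This also stands, so the protocol's silence on the method is not part of the point. Such values replace a measurement by a rule, however; they do not restore the score.

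A reader might also infer that Section 5.3 removes cannabis users. It does not: it advises them to consider leaving, and Section 9.3 excludes them only from the secondary analysis. Nor do the documents show that cannabis use for uncontrolled pain is likelier on placebo; informative losses there would offset the bias.

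**Conclusion.** The contradiction between the Section 6.1.2 schema and Section 7.1 is real and bears on the primary endpoint. Section 5.3 adds to it more weakly. If the schema is followed, the intention-to-treat comparison loses randomised participants for a reason the protocol itself expects more often on dronabinol.

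The size is unknown. The range of about 0.4 to 2.2 points on a 5-point target assumes that 7 to 12 of 35 dronabinol participants are lost, that they would on average have done 2 to 6.5 points worse than that arm's completers, and that placebo losses are uninformative. None of these values is in the protocol, and fewer or less informative losses shrink the bias in proportion.

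Two stronger readings are not supported. One is that the primary analysis is already a completer analysis with 20% of participants lost for reasons tied to arm and outcome: the 20% is an all-cause allowance, and Section 7.1 points the other way. The other is that the effect would be overstated by 25% (5.0 against 0.8 × 5 = 4.0 points). That is the single case of 7 of 35 lost with no benefit at all, an illustration and not an estimate.

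**What to change.** Reconcile the Day-2 option in Section 6.1.2 and the advice in Section 5.3 with Section 7.1, so that stopping study drug and leaving study follow-up are separate events in the text and in the case report form. State that the week-4 and week-8 outcomes already scheduled are collected for all randomised participants who do not withdraw consent, on drug or off it, and that these participants form the intention-to-treat set.

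The change concerns data collection only. It should leave every dose and every rule on when drug is stopped as it is, and the rewording of Section 5.3 should not turn advice about leaving the study into advice about stopping drug.

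The cost is a wording amendment and a few more visits or calls for participants off drug. The choice of a mixed model and of sensitivity analyses can be left to the statistical analysis plan. A mixed model alone would not solve the problem, because someone who leaves on Day 2 contributes no post-baseline score to it.

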## 4.3 Justification for Dose

Dronabinol is an FDA approved drug with a good safety profile, known pharmacokinetics, and an oral formulation which is easily mimicked in a placebo formulation. Dosing. Dronabinol will be dosed twice daily. Dronabinol is eliminated in a biphasic manner, with an initial half-life of 4 hours and a terminal half-life of 25 to 36 hours.^6,50^ Decision to use twice daily dosing at an individualized dose is based both on the biphasic half-life and the dosing recommendations for appetite stimulation for which it is FDA approved. Dose titration. The dose of dronabinol will be individualized for each participant during the first week of treatment, from a minimum of 5 mg twice daily to a maximum of 10 mg twice daily. The initial dose for all participants will be 5 mg twice daily.,If it is well tolerated the dose will be increased to 10 mg twice daily. If they do not experience adverse effects, the final dose will be 10 mg twice daily. Placebo capsules will be labelled as 5.0 mg containing matching methylcellulose containing capsules.  As the study will be double-masked, dose optimization will be completed during the placebo arm as above.

Initial study doses ranged from 2.5mg twice daily to 10mg twice daily given in 2.5mg containing capsules. However, 2.5 mg capsules are no longer manufactured and only 5mg capsules are available, so the study has been modified to use 5mg capsules in doses range from 5 to 10 mg twice daily.

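### With 5 mg capsules, the Dosing Schema permits up to 40 mg/day, twice the 20 mg/day maximum in section 4.3, and its Day 1 line doubles the stated starting dose

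*Protocol*

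**What the plan says.** Section 4.3 (Justification for Dose) individualizes the dose during the first week, "from a minimum of 5 mg twice daily to a maximum of 10 mg twice daily". On the start it says: "The initial dose for all participants will be 5 mg twice daily". The increase to 10 mg twice daily is conditional on good tolerance. The section explains that the study formerly gave 2.5 to 10 mg twice daily in 2.5 mg capsules, that these are no longer made, and that "the study has been modified to use 5mg capsules in doses range from 5 to 10 mg twice daily".

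Section 6.1.1 fixes the strength: "All doses will be administered using dronabinol 5 mg/placebo capsules". It gives the start as follows: "The starting dose in all subjects is dronabinol/placebo is 5 mg twice daily up to a total of 10 mg a day". It adds: "All discussions with subjects about dosing will be conducted in terms of numbers of capsules, not mg amounts".

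The Dosing Schema in section 6.1.2 is written in capsule counts. It opens with "Day 1: Dronabinol/placebo 2 capsules twice daily". Its Day 2 line then describes all subjects as having taken one capsule twice daily and offers an increase to two. Day 3 ends titration at one or two capsules twice daily, or with discontinuation. After the maximum well tolerated dose (MWTD) has been declared, a further clause applies when the subject and a study team clinician agree: "Subsequent upward adjustments of the declared MWTD, not to exceed four capsules twice daily, are permissible".

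**The concern.** The milligram limits and the capsule counts cannot both hold for a 5 mg capsule. The schema is the part that staff would follow when titrating, and because participants hear only capsule counts, no milligram figure in that conversation would expose a wrong count.

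Two things are at stake. A participant dosed from the Day 1 line starts at the section 4.3 maximum, with no check that 5 mg twice daily is tolerated. A participant whose dose is later raised to the schema limit takes twice that maximum, a dose for which section 4.3 offers no justification.

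The protocol itself names the relevant hazards. Section 2.3.1 lists psychiatric worsening, impaired thinking, blood pressure changes (particularly at the start or on a dose change) and added sedation with central nervous system depressants, opioids among them. Section 6.5 has participants continue their existing pain medication, so some will be taking opioids at the same time.

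**Working it through.** **Inputs**
- Current capsule strength: 5 mg (sections 4.3 and 6.1.1). Section 6.3 describes each blinded active capsule as one intact dronabinol capsule inside an outer shell, so one study capsule is 5 mg.
- Former capsule strength: 2.5 mg (section 4.3).
- Starting dose: 5 mg twice daily (sections 4.3 and 6.1.1).
- Maximum dose: 10 mg twice daily (section 4.3).
- Schema Day 1: two capsules twice daily. Schema limit on later increases: four capsules twice daily (section 6.1.2).

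**Formula**

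Daily dose = capsules per dose × mg per capsule × 2 doses per day.

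**The plan's own figures**
- Section 4.3 maximum: 10 mg × 2 = 20 mg/day, which is two 5 mg capsules twice daily.
- Stated start: 5 mg × 2 = 10 mg/day, which is one 5 mg capsule twice daily.

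**The schema with each capsule strength**

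| Schema line | Current 5 mg capsules | Former 2.5 mg capsules | Stated dose | Ratio, current to stated |
| --- | --- | --- | --- | --- |
| Day 1, two capsules twice daily | 2 × 5 × 2 = 20 mg/day | 2 × 2.5 × 2 = 10 mg/day | 10 mg/day | 20/10 = 2.0 |
| Limit, four capsules twice daily | 4 × 5 × 2 = 40 mg/day | 4 × 2.5 × 2 = 20 mg/day | 20 mg/day | 40/20 = 2.0 |

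With 5 mg capsules neither line reproduces the stated dose. With 2.5 mg capsules both do.

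**Consistency within the schema**

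The Day 2 line has everyone on one capsule and allows a step up to two. That step is empty if Day 1 was already two capsules. One capsule on Day 1 agrees with the Day 2 line and with sections 4.3 and 6.1.1.

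**Supply for one two-week dispensing period**

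These figures are derived. Section 6.1.1 says only that two weeks' worth is dispensed.
- Schema limit: 4 × 2 × 14 = 112 capsules, or 112 × 5 = 560 mg.
- Section 4.3 maximum: 2 × 2 × 14 = 56 capsules, or 56 × 5 = 280 mg.

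**After correction**
- Day 1 at one capsule twice daily: 1 × 5 × 2 = 10 mg/day, as stated.
- Limit at two capsules twice daily: 2 × 5 × 2 = 20 mg/day, as stated.

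**The case against.** The strongest reply is that 40 mg/day is a permitted ceiling and not the planned dose. Titration ends at two capsules twice daily, participants are told not to exceed their declared MWTD and may take less, and any later increase needs a clinician's agreement. Section 6.3 says that staff and participants know the capsules are 5 mg, so the clinician can convert to milligrams. Section 8.3.5 discontinues study agent at grade 3 or above and allows a lower dose at grades 1 and 2. All of this is correct and makes harm less likely. None of it sets a limit: the clinician would be applying a protocol that allows four capsules, the grade 3 rule acts only after an event, and at grades 1 and 2 the participant may stay on full dose.

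A second reply is that the Day 1 line is an obvious slip, because the next line and two other sections contradict it. That is fair, and Day 1 is the lesser of the two errors. It is still the first line that staff meet, and read literally it doubles the starting dose. The four-capsule limit has no correcting line in the schema.

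Third, the explanation by carry-over from 2.5 mg capsules is an inference. It is better supported for the limit, because section 4.3 gives the former maximum as 10 mg twice daily. It is weaker for Day 1, because the former starting dose is not given. The contradiction does not depend on the explanation.

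Finally, the two-week supply figures restate the same two-fold ratio and are not separate evidence.

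**Conclusion.** The protocol is wrong as written and must be corrected. The limit on later increases is 40 mg/day against a 20 mg/day maximum, and Day 1 is 20 mg/day against a 10 mg/day start; each is a two-fold excess. The result rests only on the 5 mg capsule strength and the stated doses, and no other section reconciles them. It does not depend on how the error arose.

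Nor does it depend on the daily total in section 6.1.1. That sentence can be read as restating the starting total of 10 mg/day. Read as a maximum, it would conflict with section 4.3 as well, and the schema limit would be 40/10 = 4 times it. The sentence is ambiguous and should be reworded in either case.

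This is a matter of participant safety. How often a participant would actually be dosed above 20 mg/day cannot be judged from the protocol.

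**What to change.** - **Dosing Schema, Day 1:** one capsule (5 mg) twice daily.
- **Dosing Schema, later increases:** no more than two capsules (10 mg) twice daily. The clause then serves participants who settled on one capsule.
- **Section 6.1.1:** give a starting dose of 5 mg twice daily (10 mg/day), rising to at most 10 mg twice daily (20 mg/day).
- **Dispensing instructions:** use the same milligram and capsule figures, which means at most 56 capsules per two weeks at the maximum dose.
- **If the clinical team does want a ceiling above 10 mg twice daily:** section 4.3 must state it and justify it.

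The cost is a protocol amendment to the text and an update of any pharmacy instructions. Sample size, visits and analysis do not change.
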